## Abstract

**Background:**

Audit and feedback (AF) interventions that leverage routine administrative data offer a scalable and relatively low-cost method to improve processes of care. AF interventions are usually designed to highlight discrepancies between desired and actual performance and to encourage recipients to act to address such discrepancies. Comparing to a regional average is a common approach, but more recipients would have a discrepancy if compared to a higher-than-average level of performance. In addition, how recipients perceive and respond to discrepancies may depend on how the feedback itself is framed. We aim to evaluate the effectiveness of different comparators and framing in feedback on high-risk prescribing in nursing homes.

**Methods:**

This is a pragmatic, 2 × 2 factorial, cluster-randomized controlled trial testing variations in the comparator and framing on the effectiveness of quarterly AF in changing high-risk prescribing in nursing homes in Ontario, Canada. We grouped homes that share physicians into clusters and randomized these clusters into the four experimental conditions. Outcomes will be assessed after 6 months; all primary analyses will be by intention-to-treat. The primary outcome (monthly number of high-risk medications received by each patient) will be analysed using a general linear mixed effects regression model. We will present both four-arm and factorial analyses. With 160 clusters and an average of 350 beds per cluster, assuming no interaction and similar effects for each intervention, we anticipate 90% power to detect an absolute mean difference of 0.3 high-risk medications prescribed. A mixed-methods process evaluation will explore potential mechanisms underlying the observed effects, exploring targeted constructs including intention, self-efficacy, outcome expectations, descriptive norms, and goal prioritization. An economic analysis will examine cost-effectiveness analysis from the perspective of the publicly funded health care system.

**Discussion:**

This protocol describes the rationale and methodology of a trial testing manipulations of theory-informed components of an audit and feedback intervention to determine how to improve an existing intervention and provide generalizable insights for implementation science.

**Trial registration:**

NCT02979964

**Electronic supplementary material:**

The online version of this article (doi:10.1186/s13012-017-0615-7) contains supplementary material, which is available to authorized users.

## Background

There is evidence that how audit and feedback (AF) is designed and delivered may impact the effectiveness of the intervention [1]. However, little attention has been paid towards identifying the best way to design AF to encourage changes in clinical practice, in order to resolve discrepancies between actual and desired performance [1]. Brehaut and colleagues identified 15 suggestions for improving the effectiveness of AF but highlighted numerous areas requiring further empirical research to address outstanding uncertainty [2].

One area of uncertainty relates to the choice of the comparator that reflects desirable practice in a feedback report. Most often, the recipients’ performance is compared against the average performance achieved by those practicing in the region. However, a higher benchmark more closely representing desired care would more clearly demonstrate the discrepancy between actual and desired performance for the majority of feedback recipients. A large randomized trial demonstrated greater improvements when feedback recipients were compared to an ‘achievable benchmark’, operationalized as the median score achieved by the top 10% of peers [3], versus those compared to the median [4]. To our knowledge, as is the case with many implementation science results [5], this has never been replicated.

Another area of uncertainty relates to the ‘framing’ of feedback content [6]. For a given quality indicator, it is possible to describe performance in multiple ways. For instance, a metric may be described as the proportion of patients for whom a desirable or guideline-concordant task was achieved (e.g. patients in whom high-risk medications were avoided). Alternatively, it may be described as the proportion of patients receiving care that is generally undesirable or not concordant with guidelines (e.g. patients inappropriately prescribed a high-risk medication). To our knowledge, despite extensive literature about how framing influences health-related decisions and behaviour in other contexts [7–12], the impact of different approaches to framing performance feedback provided to clinicians has never been tested.

We have previously argued that the science of AF is ‘stagnant’ [13] and that further trials testing AF against a usual care control group will not add new knowledge to the field [1]. Further, we have proposed that implementation scientists can partner with health systems or organizations already conducting interventions such as AF to create ‘implementation science laboratories’ in which various approaches to optimize such interventions can be tested [14]. In the present article, we describe a trial testing different AF designs, embedded within an implementation science laboratory.

## Methods

This is a pragmatic, 2 × 2 factorial, cluster-randomized trial testing variations in the comparator and in framing on the effectiveness of AF to change prescribing, in the context of an existing province-wide AF intervention. An embedded mixed-methods process evaluation will explore potential mechanisms underlying the observed effects. The protocol received ethics approval from the Research Ethics Boards at the University of Toronto and Women’s College Hospital. The Ottawa Health Science Network Research Ethics Board approved the process evaluation and the economic evaluation. The trial is registered on ClinicalTrials.gov (NLM identifier: NCT02979964).

### Setting

In the province of Ontario, Canada, medically necessary services, including a broad formulary of prescription medications for those living in nursing homes, are covered under the government-run, publicly funded health plan. Health Quality Ontario (HQO) is the provincial advisor on quality in healthcare and, as such, supports ways to improve healthcare quality through quality improvement initiatives. One such initiative is HQO’s ‘Practice Reports’, whereby confidential, aggregate feedback is offered to physicians across the province about their own practice. The reports for physicians working in nursing homes are known as the Long-Term Care Practice Reports (http://www.hqontario.ca/Quality-Improvement/Practice-Reports/Long-Term-Care). The HQO reports are generated by a multidisciplinary team, including clinicians, epidemiologists, and quality improvement experts, supported by input from front-line clinicians, health services researchers, sector organizations and associations, and policy makers. HQO relies on best evidence, advice from the groups listed above, and established methods (e.g. modified Delphi process) to select and develop indicators, and generate suggested action plans to support quality improvement for the Report.

In 2015, we developed an implementation science laboratory to support the optimization of HQO’s AF initiatives. This involves a concerted effort between implementation scientists and HQO to conduct applied research that will optimize the impact of HQO’s ongoing initiatives, while simultaneously contributing novel, generalizable findings that add to the scientific literature [14].

### Intervention design: long-term care practice reports

Details on the history of the long-term care practice reports and its re-design in preparation for this study can be found in Additional file 1.

Two members of the team (LD and JP) reviewed the content of the re-designed report to identify evidence-based behaviour change techniques (BCTs) [15] that were likely to contribute to behaviour change (i.e. the ‘active content’). This process was undertaken to ensure a standardized description of the report content with the goal of contributing to the broader understanding of how to design effective AF interventions [1]. The re-designed reports included a total of five BCTs that were operationalized throughout (summarized in Table 1).

**Table 1 Tab1:** Behaviour change techniques included in re-designed reports across all trial arms

Behaviour change technique	Definition	Example of operationalization
Feedback on behaviour	Monitor and provide informative or evaluative feedback on performance of the behaviour (e.g. form, frequency, duration, intensity)	*7/72 of my residents were prescribed a benzodiazepine*
Social comparison AND Discrepancy between goal and behaviour	Draw attention to others’ performance to allow comparison with own performance AND Draw attention to discrepancies between a person’s current behaviour (in terms of the form, frequency, duration, or intensity of that behaviour) and the person’s previously set outcome goals, behavioural goals or action plans (goes beyond self-monitoring of behaviour)	*7 additional residents in my practice may be at increased risk associated with benzodiazepines (compared to Ontario long-term care physicians with lower prescribing rates)*
Information about health consequences	Provide information (e.g. written, verbal, visual) about health consequences of performing the behaviour	*How many of my residents are exposed to risks (e.g. falls) related to benzodiazepines?*
Problem solving	Analyse, or prompt the person to analyse, factors influencing the behaviour and generate or select strategies that include overcoming barriers and/or increasing facilitators	*Change ideas, worksheets and resources regarding how to implement best practices for prescribing*

Definitions taken directly from Michie et. al. [15]

### Program theory and logic model

We developed the program theory [16] for the AF intervention in a manner consistent with the hypotheses proposed, and the theory and evidence underlying these (refer to Additional file 2). We defined the intervention according to the BCTs used to target hypothesized constructs, using terminology described by the Behaviour Change Technique Taxonomy v1 [15] and informed by techniques described by goal-setting theory [17], Social Cognitive Theory [18, 19], and nascent theory characterizing the role of competing priorities in healthcare professional behaviour change [20–22]. We then summarized the program theory as a path analytical model to inform the mechanistic theory-based process evaluation (Fig. 1).

**Fig. 1 Fig1:**
[figure not shown]
Theory-informed logic model. *APM* antipsychotic medication, *BCT* behaviour change technique, *BZD* benzodiazepine, *CNS* central nervous system

### Experimental conditions

All participants will be sent a version of the HQO Practice Reports (Additional file 3) which include the BCTs outlined above. For the study, we manipulated two features of the feedback which may be thought of as experimental factors: (1) the comparator (average vs top quartile) and (2) the framing of the feedback content (patients at risk vs patients safe from risk). Thus, we created four versions of the HQO Practice Reports (Table 2).

**Table 2 Tab2:** Factorial 2 × 2 diagram of trial arms

	Factor 1: Comparator [Top quartile/average]	
Factor 2: framing [Benefit framing/risk framing]	75th percentile/benefit framing	Average/benefit framing
	25th percentile/risk framing	Average/risk framing

### Factor 1: benchmark/comparator in feedback reports

Participants’ prescribing rates will be compared to either the provincial average or top performing peers (top quartile). Prior to this trial, HQO practice profiles compared performance of the recipient to provincial averages on a summary page and both provincial and regional averages on the detailed indicator pages. One of the recently published suggestions for practice feedback design is to use ‘a single comparator that effectively communicates the key message’ [2]. Comparing recipients to the top 10% of their peers is more likely to achieve this aim than comparing to the average score of all their peers [4]. However, HQO felt that a benchmark of the top 10% may risk unintended discontinuation of medications that may be actually be appropriate, rather than a careful review of medication use. The top quartile was decided to be acceptable for the purposes of the trial while maintaining the essential needs of the HQO program that avoids unnecessary harms to residents in LTC.

### Factor 2: framing of performance in feedback reports

Factor 2 tests the framing of the feedback reports to be either ‘risk-framed’ (e.g. emphasizing patients at risk of harms) or ‘benefit-framed’ (e.g. emphasizing patients *safe* from risk of harms) without changing the underlying data. Decision-making is affected by the way a problem (or in this case, feedback) is framed [11, 23]. Framing has been shown to affect clinical decision-making of physicians in prior studies [24], with the perceived level of risk involved in the decision posited as a mediating factor [25]. Prospect theory describes how people may differentially weigh the potential gains and potential losses, emphasizing the importance of risk aversion in decision-making [26].

We operationalized *risk framing* by providing feedback on the proportion of patients receiving high-risk medications and describing this as patients *at risk of harm* from those medications. This framing was designed to be presented in two ways: visually using the line graph with percentage of patients at risk on the *y*-axis and red colour emphasis in the graph and in text form with the statement ‘Nn additional/fewer resident(s) in my practice may be/are at increased risk associated with benzodiazepines’ (see Additional file 4). We operationalized *benefit framing* by providing feedback on the (1-X)% of patients in whom high-risk medications were avoided and described this as patients *safe from the risks of harm* associated with those medications. This framing was designed to be presented in two ways: using a line graph with percentage of patients safe from risk on the *y*-axis and green colour emphasis in the graph and in text form with the summary statement ‘No additional/fewer resident(s) in my practice may be/are safe from risks associated with benzodiazepines’ (see Additional file 4).

We refined the language for risk framing and the associated colour changes iteratively through a user-testing process (Additional file 1) to ensure that the emotional responses invoked would encourage action rather than distract from the task of improvement [6].

### Eligibility

Physicians who (1) voluntarily signed up to receive an HQO Practice Report prior to randomization and (2) consistently have >5 residents that they care for in the nursing home setting (to allow for adequate data capture) will be included in the trial. We will include data from nursing home residents if the residents’ most responsible physician is eligible.

### Allocation

Cluster randomization is necessary because the intervention is delivered to physicians who may work collaboratively with other health care professionals. To prevent contamination that could occur when physicians work in multiple nursing homes, we have grouped homes that share physicians into clusters. Thus, the unit of randomization will be groups of one or more nursing homes sharing physicians. An independent statistician will randomize these clusters independently by the two factors (resulting in four experimental conditions), stratifying by total number of beds in the cluster [27], using a randomly permuted block design of length four. Physicians who sign up for the report after randomization and who belong to a cluster already assigned will be provided the same allocation as others in their group to avoid contamination.

### Blinding

Participants in this study (i.e. physicians) are not explicitly blinded, but the risks in this instance are felt to be minimal, as they will not be aware of the variations being tested nor the outcome measures and analytical approach. Further, the trial occurs in the context of a newly designed report that incorporates new quality indicators. The analysts will be blind to allocation status.

### Data collection

Quality indicators collected for use in the feedback reports and related clinical measures are derived from routinely collected administrative data, linked using unique encoded identifiers at the Institute for Clinical Evaluative Sciences (ICES).

Data will be compiled from the following databases: (1) the Ontario Drug Benefits (ODB) database, covering nearly all prescriptions in nursing homes; (2) the Canadian Institute for Health Information (CIHI) databases covering all inpatient hospitalizations and emergency department visits; (3) the Ontario Health Insurance Plan (OHIP) database, covering physician billings; (4) the Registered Persons Database (RPDB) covering demographic information including date of death; and (5) the Continuing Care Reporting System (CCRS) database for clinical and demographic information on nursing home residents collected using the Resident Assessment Instrument (RAI). The RAI is legislatively required for each nursing home resident in the province within 2 weeks of admission date and then every 92 days, or any other time when the clinical condition of a resident considerably changes. The RAI captures a range of data such as functional and cognitive performance scales and can be used to determine date of admission and discharge from each nursing home [28].

HQO will track the unique College of Physician and Surgeons of Ontario (CPSO) numbers for those physicians who signed up for the reports. This will be encrypted and linked to the ICES Physician Database to assess physician characteristics, including age, sex, and whether they graduated from Canada or an international school. For each physician who signs up for the Practice Reports, HQO will also keep a file to track the number of times they downloaded the report at each quarterly release. This data will be confidentially shared with ICES analysts (keeping investigators blind), and the coded data will be used to conduct a sensitivity analysis to examine how intensity of exposure relates to effect size.

### Outcomes

All primary and secondary outcomes of interest are summarized in Table 3 and are defined at the individual resident level. The primary outcome is the monthly number of CNS-active medications per resident, as determined from the ODB database. ‘CNS-active’ medications will be defined in a manner consistent with the HQO quality indicator used in the Practice Reports, covering the medication classes of antipsychotics, opioids, benzodiazepines, and antidepressants (including tricyclic antidepressants and trazodone). This was chosen as a way of capturing any change to prescribing that was directly influenced by the measures provided in the Practice Reports. Secondary prescribing outcomes will include additional measures of prescribing that might be directly influenced by the Practice Reports: proportion of days supplied benzodiazepines, any prescription of benzodiazepines, mean daily benzodiazepine dose, dose equivalent of benzodiazepine dispensed, proportion of days supplied antipsychotics, any prescription of antipsychotics, mean daily antipsychotic dose, dose equivalent of antipsychotic dispensed, and presence of three or more CNS-active medications. We will also assess statin prescriptions as a non-targeted control or ‘tracer outcome’ [29]. These are not expected to be affected by the intervention and will be used to identify secular trends in prescribing in the homes.

**Table 3 Tab3:** Primary and secondary outcomes—all defined at the level of the individual resident

Outcomes	Scale	Number of repeated measurements
Primary outcome measure		
Number of CNS-active medications (antipsychotics, opioids, benzodiazepines, or antidepressants (including tricyclic antidepressants (TCAs) and trazodone))	Continuous	Monthly
Secondary outcome measures		
Benzodiazepine (or z-drug) prescription		
Proportion of days supplied	Continuous	Over the 6-month interval
Any prescription of	Binary	Monthly
Mean dose dispensed	Continuous	Monthly
Antipsychotic prescription		
Proportion of days supplied	Continuous	Over the 6-month interval
Any prescription of	Binary	Monthly
Mean dose dispensed	Continuous	Monthly
Presence of 3+ CNS-active medications: antipsychotics, opioids, benzodiazepines, or antidepressants (including TCAs and trazodone)	Binary	Monthly
Statin—tracer outcome	Continuous	Over the 6-month interval
Proportion of days supplied		

RAI data will be used to identify dates of admission and discharge to define the appropriate set of residents contributing to each time period. We will also use RAI data to summarize relevant demographic and clinical characteristics of the cohort of nursing home residents cared for the participating physicians. We will use an open cohort design; all eligible residents present in the home at any observation time will be included in the analysis. To be eligible for analysis, the most responsible physician of the nursing home resident must have signed up to receive the report.

### Analysis

All primary analyses will be by intention-to-treat. The primary outcome (monthly number of CNS-active medications over 6 months pre- and post-intervention) will be analysed using a general linear mixed effects regression model; time will be specified as a continuous variable and a common secular trend will be imposed across all study arms with the effect of the intervention modelled as a slope deviation from the secular trend. The analysis will adjust for the size of each home as a fixed effect. Random intercepts and slopes for time will be specified for the unit of randomization (group of homes) and for the individual resident to account for cluster and individual autocorrelation. The primary comparison between the arms’ 6-month post-intervention will be estimated using least square mean differences, together with 95% confidence intervals. Because the traditional two-stage testing approach (i.e. an interaction test followed by dropping the interaction term if non-significant) can lead to bias in factorial trials [30], we will present both four-arm and factorial analyses.

We will examine whether the language in the key message in the report (i.e. the bolded statement declaring the number of additional/fewer patients are at risk from (or safe from risks of) benzodiazepines) is differentially associated with changes in prescribing. This is an uncontrolled element of the intervention, dependent on the observed distribution of performance of physicians relative to their peers. The relative performance of the physician compared to the comparator may act as an effect modifier because having additional patients at risk of harm or fewer patients safe from harm may invoke different responses than having fewer patients at risk or more patients safe. Additionally, it is plausible that recipients may respond more actively to simpler language (e.g. ‘7 additional residents in my practice may be at increased risk of harm’ may be easier to interpret than ‘7 fewer residents in my practice are safe from risk of harm’) because the simpler wording may make it easier for recipients to evaluate their performance relative to the comparator and respond accordingly. Thus, we will adjust for relative performance (i.e. better, same, or worse than comparator) and clarity of the statement (i.e. additional versus fewer) as a covariate and then conduct planned subgroup analyses to examine differential effects of the intervention across these subgroups (while acknowledging unmeasured confounding and uncertain power in these subgroup analyses).

We will also explore potential effect modification by baseline prescription rate, ownership status of nursing home, beds in the home, location (urban/rural), specialist utilization (proportion of patients with geriatrician or psychiatrist consultation within 6 months), plus primary physician characteristics (sex, years’ experience), as well as patient characteristics (age, sex, time at facility, levels of function and cognition). A planned sensitivity analysis will examine effects by extent of exposure to the intervention (i.e. fidelity of receipt, which assesses whether physicians downloaded their report).

The secondary outcomes, measured as proportion of days supplied with each prescription over the 6-month interval post-intervention, will be analysed using a general linear mixed effects regression with baseline proportion as a covariate. Random intercepts will be specified for the unit of randomization and for the individual resident. Monthly mean dose dispensed will be analysed as described for the primary outcome. Secondary outcomes measured as repeated binary proportions will be analysed as described for the primary outcome but using mixed effects logistic regression.

The RAI is needed to have accurate dates of admission and discharge from nursing homes, but linking data with the RAI can involve substantial delays. A planned interim analysis will be conducted using ODB data only to be used for HQO’s internal purposes.

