### Power

In head-to-head trials where small changes to existing initiatives are tested and where each sequential change in the process of optimization is expected to offer cumulative benefit, it is necessary to power for small changes. In this pragmatic trial, the sample size is dependent on the number of providers who sign up for the reports. At the time of study launch, there will be physicians working in over 200 nursing homes who have signed up to receive the HQO Practice Reports. After grouping homes sharing providers together, we anticipate having approximately 160 clusters, with an average of 350 beds per cluster. In a 2 × 2 factorial design assuming no interaction and similar effects for each intervention, a test of each intervention at 6 months in an ANCOVA design will achieve 90% power to detect an absolute mean difference of 0.3 in the primary outcome (i.e. a reduction across arms in the mean number of CNS-active medications from 3 to 2.7). Based on previous data, we have assumed a standard deviation of 4, an intracluster correlation coefficient of 0.05, a cluster autocorrelation of 0.8, and an individual autocorrelation of 0.9 [31]. In the presence of an interaction effect, switching to a 4-arm comparison would require a slightly larger difference of 0.4 in the mean number of medications.

For our secondary outcome (any monthly prescription of antipsychotics), our sample size will achieve 90% power to detect an absolute difference of 1.2% (or a relative difference of 6%) from a reference arm proportion of 20% using six monthly pre- and post-intervention measurements, with an intracluster correlation coefficient of 0.05, a cluster autocorrelation of 0.8, and an individual autocorrelation of 0.9. In the presence of an interaction effect, switching to a 4-arm comparison would require a larger relative difference of 8.5%.

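### Randomisation is stratified by total beds in the cluster, but the primary model adjusts for the size of each home and the days-supplied models name no size term (minor)

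*Protocol article*

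**What the plan says.** The Allocation section of the protocol article defines the randomised unit: "the unit of randomization will be groups of one or more nursing homes sharing physicians". It then gives the restriction on randomisation: "stratifying by total number of beds in the cluster [27], using a randomly permuted block design of length four". The stratifier is thus a cluster-level total.

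The Analysis section says of the primary model: "The analysis will adjust for the size of each home as a fixed effect". The next sentence sets the random effects: "Random intercepts and slopes for time will be specified for the unit of randomization (group of homes) and for the individual resident". Neither the stratum nor total beds in the cluster is named as a covariate.

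Later in the Analysis section, monthly mean dose and the monthly binary outcomes are to be analysed as the primary outcome is (by logistic regression for the binary ones), so by reference they carry the home-size term. The days-supplied outcomes (benzodiazepine, antipsychotic and the statin tracer) have their own model: baseline proportion as covariate and random intercepts, with no size term named.

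On scale, the Power section refers to "physicians working in over 200 nursing homes who have signed up to receive the HQO Practice Reports" and adds that "we anticipate having approximately 160 clusters, with an average of 350 beds per cluster".

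**The concern.** When randomisation is balanced within strata, the analysis should normally condition on those strata. Otherwise the between-stratum variation that the design removed from the treatment comparison stays in the error term. Standard errors are then somewhat too large and tests somewhat conservative.

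Here the covariate sits at a different level from the stratifier. Two small homes sharing a physician can form a cluster in a large-bed stratum, and the size of either home does not recover that stratum. Loose wording is possible but not the natural reading: the Analysis section itself separates the home from the group of homes, and it lists beds in the home among the possible effect modifiers. No reason is given for the change of level.

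What is at stake is a little precision and agreement between design and analysis. The treatment effect is not biased by it.

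**Working it through.** **1. The plan's own figure.** The Power section states that "a test of each intervention at 6 months in an ANCOVA design will achieve 90% power to detect an absolute mean difference of 0.3", assuming "a standard deviation of 4, an intracluster correlation coefficient of 0.05, a cluster autocorrelation of 0.8, and an individual autocorrelation of 0.9". With m = 350 and 80 clusters per level of each factor:

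- 1 + (m − 1) × ICC = 1 + 349 × 0.05 = 18.45
- r = (350 × 0.05 × 0.8 + 0.95 × 0.9) / 18.45 = 14.855 / 18.45 = 0.805
- design effect = 18.45 × (1 − 0.805²) = 6.49
- effective n per level = 80 × 350 / 6.49 = 4,315
- SE = 4 × √(2 / 4,315) = 0.0861
- detectable difference at 90% power, two-sided 5% (alpha is an assumption; the article gives 95% confidence intervals) = (1.960 + 1.282) × 0.0861 = 0.279

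This rounds to the stated 0.3, where power is 93.6%. The four-arm figure comes out at 0.395 against the stated 0.4. No size covariate enters, so the power statement is untouched by this point.

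**2. How often the two size variables differ.** With H homes in K clusters, at most H − K clusters can hold more than one home, so at least 2K − H are single-home. For K = 160:

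| Homes | Single-home clusters, at least |
|---|---|
| 200 | 120 (75%) |
| 220 | 100 (62.5%) |
| 240 | 80 (50%) |

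The article says only that there are over 200 homes, so 120 is the floor at exactly 200.

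**3. Home size against the stratum, general cluster-level check.** Simulation of 4,000 trials per scenario, 160 clusters, blocks of four within strata. Assumptions: four bed strata, 40 or 60 two-home clusters, lognormal home sizes, correlation 0.1 to 0.5 between log cluster beds and outcome, no baseline adjustment.

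| Size term in model | Type I error |
|---|---|
| none | 2.3–5.2% |
| home size | 4.1–5.6% |
| bed strata | 4.5–5.4% |
| total beds, continuous | 4.6–5.4% |

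Log home size and log cluster beds correlated at about 0.86 to 0.89. In the worst scenario the mean SE with home size was 0.1426, against 0.1392 with strata (ratio 1.024) and 0.1366 with continuous total beds (ratio 1.044).

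**4. The primary model.** The planned model has six pre and six post months, a common secular trend, the effect as a slope deviation, and random cluster intercepts and slopes. A stratum main effect explains only level differences between clusters. Generalised least squares on cluster means used the Power section's inputs, with assumed cluster slope variance 0.0005 to 0.01 and cluster-month variance 0 to 0.16. Removing 5 to 15% of the cluster intercept variance (assumed to be what the strata explain) reduced the SE of the 6-month effect by at most about 0.2%.

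**5. The days-supplied models, no size term.** In the simulation, omitting size altogether gave SE ratios against strata of 0.1578 / 0.1571 = 1.004, 0.1579 / 0.1514 = 1.043 and 0.1579 / 0.1392 = 1.134 at correlations 0.1, 0.3 and 0.5. Those runs had no baseline covariate; the planned models do. If cluster beds correlate g with both the baseline and follow-up cluster means, and these correlate r = 0.805 (the primary outcome's value, borrowed as an assumption), the partial correlation is g(1 − r) / √((1 − r²)(1 − g²)), and the SE ratio is 1 / √(1 − partial²):

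- g = 0.3: partial 0.103, ratio 1.005
- g = 0.5: partial 0.190, ratio 1.018

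**The case against.** The strongest reply is that the plan already has a bed-size covariate. In single-home clusters it is the stratifier, and elsewhere it is closely correlated with it. The primary model's pre-period data and random intercepts absorb most level differences in any case. This is also a condensed article whose analysis plan is not shown, and covariate coding is often settled there.

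Most of that stands. A reader might infer that the stratification is ignored altogether, or that the covariate used was left unbalanced. The documents do not support either reading for the primary model, because home size is a close and therefore partly balanced proxy. A reader might also apply 1 / √(1 − R²) with R² of 5 to 15% and expect standard errors 3 to 8% too large. That formula compares adjustment with no adjustment. The plan adjusts for a proxy, and step 4 shows that the slope model hardly responds to level differences.

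Two things remain. The article does not leave the size covariate open: it names one, at a level that was not stratified. And the proxy argument does not reach the days-supplied models, which name no size term.

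**Conclusion.** The mismatch is real and minor. Home size stands in for the stratifier in the primary model, and in the secondary models that follow it; the days-supplied models have neither.

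The consequence is slight conservatism: probably negligible for the primary slope model and probably about 2% of the SE at most for the days-supplied models after baseline adjustment. The second figure assumes a correlation of no more than 0.5 between cluster beds and outcome, and a cluster-level baseline correlation near 0.8. With weaker baseline adjustment, for instance where newly admitted residents have little baseline data, the loss would lie between that and the unadjusted ratios in step 5. Neither bias nor any change to the stated power follows. The actual number of strata, the mix of cluster sizes and the link between beds and prescribing are not given, so all sizes here rest on assumed values.

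**What to change.** Name the randomisation stratum (or total beds in the cluster) as a fixed effect in the primary model and in every secondary model, including the days-supplied models. Home size can stay as an additional covariate. If the size of each home was meant to denote total beds in the cluster, say so and extend the term to the days-supplied models.

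The cost is nil. The stratum is in the randomisation file, no new data are needed, and the sample size is unaffected. The Trial status section reports allocation complete and the intervention ongoing, so the change can be fixed before the outcome analysis.
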